### Secondary outcome indicators

3.2

The most important secondary outcome measurement is the improvement of WOMAC function in week 4. We will also assess the total score, function score and stiffness score of WOMAC at baseline, weeks 2, 8, 12, and 24. Visual analog scale pain score will be used to evaluate the arthritis pain of subjects at baseline, weeks 2,4, 8, 12, 24. SF-36 will be used to measure the quality of life of the subjects in the 4th, 12th, and 24th week. In addition, we will evaluate the efficacy of a 5-point scale in the fourth week (1 = very poor, 2 = poor, 3 = general, 4 = OK, 5 = very good.).

Any adverse event, whether related to treatment, requires the subject and investigator to report on each treatment or visit. Side effects include redness and blisters by Jade moxibustion and traditional moxibustion. Serious adverse events will be reported to the Ethics Committee. During the follow-up period (week 5 to week 24), we will call the subject weekly to find out about the adverse reactions and side effects that may occur during the week.

After 4 weeks of treatment, investigator will ask the subjects about the safety of the treatment: safe, fewer safe, have safety problem, and have serious safety problem. After each treatment we will ask the subject's feeling: “What do you feel during the treatment? 1. Heat; 2. Cold; 3. Pain; 4. no feeling; 5. Other, please describe”

The subjects will be allowed to take the analgesic or non-steroidal anti-inflammatory drugs used before the test, we will ask subjects to record the daily dose during the entire clinical trial, and then analyze the changes in the dose.

We will measure the outcome of the baseline, week 2, 4, 8, and 12 at the hospital. For the outcome of Week 24, we will mail the questionnaire to the subjects and ask them to post them back after filling them out.

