**Methods/Design::**

This is a 2-parallel-group, randomized controlled trial. A total of 148 subjects with KOA (Kellgren–Lawrence grade II or III) will be recruited and randomized to receive Jade moxibustion treatment or a traditional moxibustion treatment in a 1:1 ratio. Jade moxibustion group: The affected knee of the subjects will be covered with jade kneepad. Traditional moxibustion group: Chosen the ST35, ST34, EX-LE4, SP10 and Ashi points at the affected knee. The subjects will receive treatment three times a week, altogether 12 times in 4 weeks. The main outcomes are WOMAC knee pain score, knee function score and SF-36 quality of life questionnaire changes at the 4th week. Secondary outcomes include WOMAC knee pain score and knee function score, overall clinical efficacy evaluation, medication, safety evaluation at the 2nd, 12th, and 24th week, and cytokines related to osteoarthritis in serum.

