### Primary outcome indicators

3.1

The primary outcome measure is the change in pain relative to baseline at the Western Ontario and McMaster Universities Osteoarthritis Index (WOMAC) in 4 weeks. The most painful knee joint for the subject will be recorded at the baseline, which will be the joint we measured throughout the trial. We will also measure WOMAC pain at week 2, 8, 12, and 24.

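### Section 3.2 lists SF-36 only at weeks 4, 12 and 24, although the abstract defines the SF-36 outcome as a change at week 4

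*Protocol article*

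**What the plan says.** The abstract (Methods/Design) lists the main outcomes: "The main outcomes are WOMAC knee pain score, knee function score and SF-36 quality of life questionnaire changes at the 4th week".

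The body differs. Section 3.1 gives a single primary outcome: "The primary outcome measure is the change in pain relative to baseline at the Western Ontario and McMaster Universities Osteoarthritis Index (WOMAC) in 4 weeks". SF-36 appears in section 3.2, among the secondary outcomes, with this schedule: "SF-36 will be used to measure the quality of life of the subjects in the 4th, 12th, and 24th week".

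The two sentences just before it do name a baseline for other instruments:
- WOMAC: "We will also assess the total score, function score and stiffness score of WOMAC at baseline, weeks 2, 8, 12, and 24".
- VAS pain: "Visual analog scale pain score will be used to evaluate the arthritis pain of subjects at baseline, weeks 2,4, 8, 12, 24".

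Later in section 3.2 there is a general sentence on visits that names no instrument: "We will measure the outcome of the baseline, week 2, 4, 8, and 12 at the hospital". Section 3.4 refers to Table 1 for the collection timetable; that table is not shown. Section 3.6 treats SF-36 as secondary and plans an unpaired comparison of the two groups at the follow-up time points, with a t-test or rank sum test for continuous variables.

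**The concern.** A change at week 4 needs a value from before treatment. The abstract promises that change, and the one sentence that schedules SF-36 does not provide for the earlier measurement. Because baseline is written out for WOMAC and VAS in the same paragraph, a site working from this text could reasonably conclude that SF-36 starts at week 4.

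At stake is whether the SF-36 result can be reported as the abstract describes it. Without a baseline, only raw week-4 scores can be compared. That comparison is valid under randomisation, but it is less precise and gives no means of accounting for a chance imbalance in quality of life at entry. A baseline that was not collected cannot be recovered once patients have been treated.

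**Working it through.** **Step 1: does any visible text supply a baseline SF-36?**

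- *The SF-36 sentence in section 3.2:* weeks 4, 12 and 24. No baseline.
- *The general visit sentence in section 3.2:* it says where measurement takes place, since the next sentence contrasts it with the postal questionnaire at week 24. It cannot mean every instrument at every visit. That would put SF-36 at weeks 2 and 8, which its own sentence leaves out, and would put the week-4 efficacy rating before any treatment. It allows a baseline SF-36 but does not state one.
- *Section 2.6:* there is a baseline assessment, placed after randomisation, with no instruments named.
- *Section 3.6:* a between-group comparison of follow-up scores, which neither uses nor implies a baseline SF-36.
- *Table 1:* not shown, so it is unknown either way.

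The visible text therefore gives no baseline SF-36, and only the abstract's reference to changes implies one.

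**Step 2: what would a baseline be worth?**

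The plan gives no detectable difference for SF-36, so there is no figure to reproduce. Inputs:
- n = 67 per arm, from section 3.5. It agrees with 74 recruited less 10% loss: 74 × 0.90 = 66.6. Section 3.5 also gives 62, so all three sizes are shown below.
- Two-sided 0.05 and 80% power: 1.960 + 0.842 = 2.802.
- Baseline-to-week-4 correlation ρ: not in the document. Assumed values 0.5 and 0.7.

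Week-4 scores alone: 2.802 × √(2/n) SD.
Adjusted for baseline: the same, multiplied by √(1 − ρ²), which is √0.75 = 0.866 at ρ = 0.5 and √0.51 = 0.714 at ρ = 0.7.

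| n per arm | Week 4 alone | Adjusted, ρ = 0.5 | Adjusted, ρ = 0.7 |
|---|---|---|---|
| 62 | 0.503 SD | 0.436 SD | 0.359 SD |
| 67 | 0.484 SD | 0.419 SD | 0.346 SD |
| 74 | 0.461 SD | 0.399 SD | 0.329 SD |

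The variance falls by ρ², that is 25% or 49%.

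**Step 3: simple change score or adjusted comparison?**

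With equal SDs at both times, the SD of a change is √(2(1 − ρ)) times that of a single score. At ρ = 0.5 the factor is 1.000, so with 67 per arm the detectable difference stays at 0.484 SD. At ρ = 0.7 it is 0.775, giving 0.375 SD. Collecting the baseline makes the abstract's change computable; most of the precision comes from adjusting for it.

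**The case against.** The strongest reply is that the schedule proper is in Table 1. An article condenses the full protocol, and a sentence listing follow-up weeks need not repeat the baseline. The lists in section 3.2 are also loosely drafted: the WOMAC list omits week 4, although week-4 function is the leading secondary outcome. And the SF-36 analysis in section 3.6 can be run without any baseline.

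Much of this stands. A reader might infer that a main outcome of the trial cannot be computed. The document does not support that, for three reasons: Table 1 may list a baseline SF-36, the body makes WOMAC pain the sole primary outcome, and the planned unpaired comparison needs only follow-up scores. Nor can it be said that section 3.2 would contradict a table that includes baseline. The sentence does not exclude other time points, so it would be incomplete and should be aligned.

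The precision figures measure the value of a better analysis. They are not an error in a stated figure, and collecting the baseline alone would not deliver them, because section 3.6 plans no adjustment.

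What does not stand is the argument from the WOMAC list as applied to function. That list adds to a sentence which has already fixed function at week 4. (WOMAC total and stiffness at week 4 are not covered, so the drafting is indeed uneven.) No other sentence in the body supplies an SF-36 baseline.

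**Conclusion.** The inconsistency is real but modest. The abstract defines the SF-36 outcome as a change, and the only visible SF-36 schedule names no baseline. If that sentence governs, neither the change nor a baseline-adjusted comparison is available; if Table 1 lists a baseline, the defect is one of wording. Either way section 3.2 needs correcting.

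The point concerns a secondary outcome unless the sponsor confirms the abstract, and the conflict over the status of SF-36 should be settled at the same time.

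In size, with 67 per arm, the detectable difference is 0.48 SD without a baseline, against 0.42 SD or 0.35 SD with adjustment. This rests on assumed correlations of 0.5 and 0.7, a linear relation between baseline and week-4 scores, and a two-sided test at 0.05 with 80% power. The article gives no non-inferiority margin for SF-36, but confidence interval widths shrink by the same factors.

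**What to change.** 1. In section 3.2, state that SF-36 is measured at baseline, before the first treatment, and in weeks 4, 12 and 24.
2. Preferably take the baseline SF-36 before allocation is known, because patients complete it themselves and cannot be blinded to these two treatments. Section 2.6 now places the baseline assessment after randomisation, so that step would have to be reordered.
3. Check the sentence against Table 1 and make the two agree.
4. In section 3.6, compare week-4 SF-36 between groups adjusted for the baseline score (analysis of covariance), in place of the unpaired test.
5. Give SF-36 the same status in the abstract and in sections 3.2 and 3.6.

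The cost is one questionnaire at an assessment that already exists, a few minutes per patient, plus short text changes and the reordering in section 2.6. If patients have already been treated without a baseline SF-36, the change cannot be reported for them. The article should then say so and describe the outcome as the week-4 score.

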### Exploratory outcome indicators

3.3

Exploratory outcome is the levels of IL-1β, COX-2, COMP, tumor necrosis factor IL-1α, IL-6, IL-17, IL-8, IL-4, IL-10, and IL-13 in serum. Interleukin-1b is a key virulence factor for osteoarthritis.^[34]^ IL-6, IL-8 and tumor necrosis factor alpha (TNF-A) play a role in pain during exercise, whereas TNF-A plays a role in pain at rest. The levels of Serum IL-16 were significantly associated with the WOMAC scores and their subfractions of KOA procedures and time commitments.^[35]^ The 5 ml fasting venous blood will be obtained before treatment and 4 weeks after treatment. After standing, the serum will be centrifuged, and the tubes will be placed in a refrigerator at −80°C for testing. The changes in the above markers in serum will be detected by enzyme-linked immunosorbent assay (ELISA) and Human Cytokine Array Kit. In order to reduce the influence of the circadian rhythm, each blood draw will take place between 10 and 11:30 in the morning. We will use the human cytokine array kit from R&D Systems to analyze osteoarthritis-associated cytokines in subjects’ serum. In addition to detecting the IL-1β, TNF-α, IL-6, IL-17, IL-8, IL-4, IL-10, and IL-13 cytokines, the kit can also detect additional 28 cytokines, so we can also explore whether other factors are involved in the pathogenesis of osteoarthritis.

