### Study design

2.1

This trial is a non-inferiority randomized controlled clinical trial, which is designed to compare the clinical efficacy of the Jade moxibustion and traditional moxibustion in treating typical inflammatory pain–KOA. The protocol has been registered on ISRCTN registry (No 21174552) and will be conducted in accordance with the Declaration of Helsinki.

The study flow outline is shown in Figure 1

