### Randomization

2.6

A total of 148 subjects with KOA who are eligible per protocol will be randomly assigned to group A - Jade moxibustion group or group B - traditional moxibustion group in a 1:1 ratio. The subject will first receive a brief phone consultation, after that, the subject will be allocated to the site. After the investigator and the subject signed the informed consent, the investigator will perform a simple rheumatic examination. The investigator will make a diagnosis based on the knee x-ray film brought by the subject or the knee X-ray performed at site. Only the subject who meet the inclusion/exclusion criteria will be randomized by central network randomization program. Then investigator will make baseline assessment and arrange treatment.

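### Section 3.3 gives the 28 extra array cytokines a pathogenesis question, but every sample comes from a patient with knee osteoarthritis and no comparison that could establish involvement in pathogenesis is described (minor)

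*Protocol article*

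**What the plan says.** Section 3.3 opens with the named markers ("Exploratory outcome is the levels of IL-1β, COX-2, COMP" and a list of interleukins and tumor necrosis factor). It fixes two blood draws: "The 5 ml fasting venous blood will be obtained before treatment and 4 weeks after treatment". On measurement it says: "The changes in the above markers in serum will be detected by enzyme-linked immunosorbent assay (ELISA) and Human Cytokine Array Kit". It then turns to the array: "We will use the human cytokine array kit from R&D Systems to analyze osteoarthritis-associated cytokines" in the subjects' serum. After naming eight cytokines that the array covers, it adds that "the kit can also detect additional 28 cytokines", and closes with the reason for using them: "so we can also explore whether other factors are involved in the pathogenesis of osteoarthritis". No other purpose is given for these 28 analytes.

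The samples come from the trial population alone. Section 2.6 (Randomization) says: "A total of 148 subjects with KOA who are eligible per protocol will be randomly assigned". Section 2.3 makes the diagnostic criteria for KOA and radiologic confirmation conditions of entry. Section 2.8 gives both arms active heat treatment. Section 2.1 describes the trial as "designed to compare the clinical efficacy of the Jade moxibustion and traditional moxibustion in treating typical inflammatory pain–KOA".

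**The concern.** To say that a factor takes part in the pathogenesis of a disease, one needs at least a contrast that bears on the disease arising or advancing: people with it against people without it, people before and after onset, or people whose joints deteriorate against people whose joints do not. The clause in section 3.3 names such a question, but the design described around it contains none of these contrasts.

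What is at stake is interpretation. The extra analytes have no other stated purpose, so any of the 28 that moves between the two draws, or differs between patients, could be reported under the only heading the plan offers, which is disease mechanism. A plan that states the answerable questions beforehand removes that temptation.

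**Working it through.** No figure in the plan needs to be reproduced, because the point does not depend on alpha, power, margin or event rates. The check sets the stated question against the contrasts that the design supplies.

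**Inputs**
- Patients: 148, all with KOA, randomised 1:1 (section 2.6); 74 per arm (section 3.5).
- Entry: KOA diagnosed and confirmed on X-ray, with a pain score of 40 or more on the visual analog scale (section 2.3). The Abstract and section 2.3 give different radiographic grades, but on either version the disease is required.
- Arms: Jade moxibustion and traditional moxibustion, both active (section 2.8).
- Draws: two per patient, one before treatment and one after (section 3.3).
- Array: eight named cytokines plus 28 others, so 8 + 28 = 36 analytes (section 3.3).

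**Count of samples**
- Maximum: 148 × 2 = 296.
- Before trial treatment: up to 148.
- After it: up to 148, and fewer if the 10% loss allowed for in section 3.5 occurs.
- From people without osteoarthritis: 0.

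**Which contrasts exist**

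| Contrast | In the design? |
|---|---|
| Osteoarthritis v no osteoarthritis | No: disease is an entry condition |
| Before v after disease onset | No: all have the disease at entry |
| Structural progression v none | None described: X-ray appears only for diagnosis at entry (sections 2.2 and 2.6), and sections 3.1 to 3.3 list no structural outcome |
| Treated v untreated or sham | No: both arms are active |
| Jade v traditional moxibustion | Yes, randomised |
| Marker level v symptoms within KOA | Yes, observational |
| Change from before to after treatment | Yes, but without an untreated control |

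The first three rows are the ones that bear on pathogenesis, and none is available. The last row does not fill the gap. Natural course, regression to the mean after selection on a pain threshold, and the permitted analgesics and anti-inflammatory drugs (sections 2.8 and 3.2) can all act between the draws, alongside the treatment. Randomisation protects the comparison between arms from these, but not the change within an arm.

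**The between-arm comparison**

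Section 3.6 does not name the serum markers. The only sentence there that would reach them is the general one for continuous variables, a t-test or Wilcoxon rank sum test, with no baseline adjustment. For a marker with the same standard deviation σ at both draws, correlation ρ between draws and n patients per arm, the variance of the estimated difference between arms is:
- post-treatment value alone: 2σ²/n;
- change from baseline: 2σ²/n × 2(1 − ρ);
- baseline-adjusted: about 2σ²/n × (1 − ρ²).

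Since 1 − ρ² is never above 1, and 2(1 − ρ) − (1 − ρ²) = (1 − ρ)² is never negative, the adjusted estimate is in large samples at least as precise as either alternative. It uses a baseline sample that is drawn anyway. The unadjusted test remains valid in a randomised comparison; it is only less efficient.

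**The case against.** The strongest reply is that the text claims little. The verb is to explore, the heading is exploratory, and the sentence reads as a closing remark on what the kit can detect. The aims in the Abstract, section 2.1 and the Discussion concern clinical efficacy and non-inferiority, and none mentions pathogenesis. Pre-treatment levels can be related to pain or severity within KOA, and section 3.3 itself cites such a link, between serum IL-16 and WOMAC scores. This stands as far as it goes: such work can generate hypotheses, and it makes the point minor. It does not remove the point. An exploratory label lowers the certainty expected but does not supply a missing comparator, and an association with symptoms in people already affected is a different question from involvement in pathogenesis. The Abstract also lists serum cytokines among the secondary outcomes, so the exploratory status is not uniform.

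Three stronger readings are tempting, and the document does not support them.
- A reader might infer that the samples fail because all come from treated patients. The first draw precedes treatment, so up to 148 of 296 do not. The reason is that all come from patients with the disease.
- A reader might infer that the plan intends many uncontrolled before-after tests, one per marker in each arm. No within-arm cytokine test is planned. Section 3.3 speaks only of detecting changes, and the comparisons in section 3.6 are between groups.
- A reader might infer that the array data have no use. They support a randomised comparison and associations within KOA.

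**Conclusion.** The point holds as a minor one. The clause in section 3.3 attaches a pathogenesis question to 28 analytes, and the design described has no contrast that could establish an answer: 0 of at most 296 samples come from people without osteoarthritis, there is no untreated arm, and neither onset nor structural progression is observed. The data can compare the two arms and can generate hypotheses about associations within KOA. The primary outcome, sample size, randomisation and error control are unaffected.

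The conclusion assumes that the visible outcome sections are complete on this matter. The data collection timetable (Table 1) is not shown. If it contains a structural outcome or a reference group mentioned nowhere in the text, the conclusion would have to be revisited. It does not depend on whether the second draw falls at the end of the four-week course or four weeks after it.

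**What to change.** Replace the pathogenesis clause in section 3.3 with wording such as:

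> For each serum marker we will estimate the difference between groups in the post-treatment level (or in the change), adjusted for the baseline value. We will also explore the association of marker levels and changes with WOMAC pain among patients with KOA. These analyses are exploratory. Changes within a group are descriptive and will not be interpreted as evidence on pathogenesis.

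For the markers, the baseline-adjusted estimate would take the place of the unadjusted t-test or Wilcoxon test in section 3.6, on a transformed scale if a marker is skewed.

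The cost is a short rewording and a narrower exploratory claim. No extra samples, visits or assays are needed. Keeping pathogenesis as an aim would instead require a comparison that the design lacks, such as a reference group without osteoarthritis, which is a much larger change for one exploratory sentence.

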### Data collection and management

3.4

In order to ensure that the subjects receive a complete follow-up, all our measures are free of charge. The case report form will be completed in paper form and then entered into the spreadsheet. The original case report form and other forms (including informed consent) will be kept by the school of acupuncture and massage, Shanghai University of TCM. The required data will be collected according to the following case data collection timetable (Table 1). The Research Ethical Committee of Tongren Hospital Affiliated to Shanghai Jiaotong University will audit the trial conduct every 6 months independently of investigators and the sponsor, and will decide on any premature closure of the study.

**Table 1 T1:**
[figure not shown]
Case data collection timetable.

### Sample size

3.5

There is study indicates that at least a 36% increase in WOMAC score is considered effective.^[36]^ In the previous study of the research group, the average effective rate of the Jade moxibustion group was 55.56%, compared with 46.51% in the traditional moxibustion group. Based on the results of our pilot study and previous reports, we used non-inferiority test to calculate the sample size (α = 67 per group) with α = 0.025, 1−β = 80%, and a cutoff of 0.5. In other words, we expect a sample size of 62 subjects per group to be sufficient to detect statistically significant differences between the 2 groups. There were no cases of shedding in the 2 treatment groups in the previous trial. In order to prevent the occurrence of shedding resulting in insufficient sample size (preset 10% shedding rate), we will recruit 74 subjects for each group, and a total of 148 subjects need to be recruited.

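### The stated non-inferiority cutoff of 0.5 has no scale, exceeds the control rate if read as a difference in response rates, and does not reproduce the sample size of 67 (or 62) per group

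*Protocol article*

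**What the plan says.** Section 2.1 (Study design) of the protocol article fixes the type of trial: "This trial is a non-inferiority randomized controlled clinical trial". Section 3.5 (Sample size) bases the calculation on the research group's own earlier study, in which "the average effective rate of the Jade moxibustion group was 55.56%, compared with 46.51% in the traditional moxibustion group". The remaining inputs are "with α = 0.025", power of 80% "and a cutoff of 0.5". No scale is attached to the cutoff, and no other margin appears anywhere in the article.

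The section then gives two group sizes. The first is printed as "calculate the sample size (α = 67 per group", where the symbol is evidently meant to be n. The next sentence says "we expect a sample size of 62 subjects per group to be sufficient". With a "preset 10% shedding rate", the plan ends at "we will recruit 74 subjects for each group, and a total of 148 subjects need to be recruited".

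Section 3.6 (Statistical analysis) compares the week-4 remission rate between groups by a chi-square test at the 0.05 level. It names no margin and no confidence limit.

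**The concern.** In a non-inferiority trial the margin defines how much worse the new treatment may be and still be accepted. Here the only margin in print sits beside two response rates, and the main analysis also compares a rate. On that scale a margin of 0.5 is larger than the control rate of 0.4651, so it excludes nothing: no possible jade response rate is too low. A margin that large should also need very few patients, which does not fit the 67 or 62 per group printed in the same paragraph.

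If the printed value stands, a reader cannot tell what the trial was powered to exclude. The true limit could also be settled after the results are known.

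**Working it through.** **Inputs (all from section 3.5 unless noted).** Jade rate p₁ = 0.5556; traditional rate p₂ = 0.4651; difference +0.0905. Power is 80% and allocation 1:1 (section 2.6). α = 0.025 is taken as one-sided, since the section does not say. The response in 3.5 and the remission rate in 3.6 are taken to be the same kind of measure, a proportion.

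**Formula for a margin d on the rate difference (unpooled variance).**

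n per group = (1.960 + 0.8416)² × [p₁(1 − p₁) + p₂(1 − p₂)] / (p₁ − p₂ + d)²

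- (1.960 + 0.8416)² = 7.849
- Variance sum = 0.2469 + 0.2488 = 0.4957
- Numerator = 7.849 × 0.4957 = 3.891

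**Step 1. Try to reproduce the plan's figure with d = 0.5.** n = 3.891 / 0.5905² = 3.891 / 0.3487 = 11.2, so 12 per group. The plan says 67, then 62. Farrington-Manning variance gives 9.2. Equal true rates give 16. At 67 per group, power for d = 0.5 would exceed 99.99%, not 80%. The figure is not reproduced.

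**Step 2. Position of the boundary.** 0.4651 − 0.5 = −0.035. A response rate cannot be negative, so every true jade rate, including 0%, lies inside the margin.

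**Step 3. Other readings of 0.5 at the pilot rates.**

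| Reading of 0.5 | n per group |
|---|---|
| Odds ratio | 56.8 |
| Risk ratio | 20.2 (log scale) to 23.2 (linear scale) |
| Half of the control rate as margin | 38 |
| Standardised mean difference: 2 × 7.849 / 0.5² | 62.8, so 63 |

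Assuming equal true rates instead, the odds ratio gives 132 to 133, the risk ratio 27 to 46, and half the control rate 72 to 73. None of these readings gives 67. Only the standardised difference comes near 62.

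**Step 4. Which group size drives recruitment.** 67 × 1.1 = 73.7, so 74, as printed. 62 × 1.1 = 68.2, so 69. The recruited number therefore follows from 67. (Dividing, 67 / 0.9 gives 75.)

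**Step 5. Which margin fits the printed sizes.**
- d = 0.15: 3.891 / 0.2405² = 3.891 / 0.05784 = 67.3. This rounds up to 68; Farrington-Manning gives 66.6, so 67.
- d = 0.16: 3.891 / 0.2505² = 3.891 / 0.06275 = 62.0.

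**Step 6. What 0.5 would do as a decision limit.** The article states no such rule, so one has to be assumed: non-inferiority is declared if the lower limit of the 95% Wald interval for jade minus traditional is above −0.5, with 67 per group and control at 46.51%. Exact binomial probabilities of declaring non-inferiority are 96.7% if jade is 20 points worse (26.51%), 47.4% if jade is at 10%, 24% at 5% and 8% at 0%. Under the same rule with a limit of −0.15, a device 20 points worse passes 0.5% of the time.

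**Step 7. Power at d = 0.15 and 67 per group.** If jade is truly 9.05 points better, power is about 80%. If both true rates are 46.51%, it is 41% by the normal approximation and 40% by exact calculation.

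**The case against.** The strongest defence is that the scale is unstated and need not be a difference in rates. Section 3.1 defines the primary outcome as a change in WOMAC pain, which is continuous, and a standardised difference of 0.5 gives 63, close to the printed 62. This part stands: the documents do not prove which scale was meant. It does not repair the paragraph, because that reading leaves the two quoted rates unused, does not give 67, does not lead to 74, and does not match a chi-square test on a rate.

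A second defence is that 0.5 is only a sample-size input. This is also correct. A reader might infer that the trial, run as written, would declare a useless device non-inferior. The article does not support that. Section 3.6 applies no margin, so the error rates in step 6 belong to an assumed confidence-limit rule. Even under that rule, a device with 10% responders passes about 47% of the time and one with none about 8%. Only the case of a device 20 points worse (97%) is striking.

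A third defence is that this is an obvious misprint of 0.15. That is plausible, but it rests on taking 67 as correct. The 62 in the next sentence points to 0.16, and a margin solved back from a sample size has no clinical justification of its own.

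Finally, an unseen analysis plan might hold the right margin. The point here is not that a margin is missing: one is stated, and a different value elsewhere would contradict it.

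**Conclusion.** The point holds in this form: the only margin printed for this non-inferiority trial has no stated scale, and none of the readings tried reproduces the operative 67 per group. On the response-rate scale that the inputs and the main analysis use, it exceeds the control rate by 3.5 points and needs 12 per group, against 67 and 62 stated. This rests on a one-sided α of 0.025 and the pilot rates as printed; one-sided values of 0.0125 and 0.05 give 14 and 9, so the conclusion does not depend on that choice.

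The article does not establish that 0.15 was intended, nor that the trial will be judged against 0.5. A reader might also conclude that correcting 0.5 to 0.15 leaves the trial adequately powered without further thought. That is true only if jade is really about 9 points better; at equal rates, power is about 40%.

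The correction should be made before any data are seen.

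**What to change.** 1. In section 3.5, replace the cutoff of 0.5 with the margin actually used, name its scale and give its justification. If 0.5 is a misprint of 0.15 on the rate difference, the sponsor should confirm this from the original calculation.
2. Reconcile 67 with 62, and correct the symbol printed in front of 67.
3. In section 3.6, state the same margin as the limit against which the confidence bound for the week-4 comparison will be judged.
4. If the margin was meant on the WOMAC score scale, redo section 3.5 on that scale with a score-based standard deviation, and align section 3.6 with it.
5. State that the power calculation assumes jade to be better by 9.05 points, and give the power at equal rates.

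Items 1 to 3 and 5 cost only text if a margin of about 0.15 was used and the assumed advantage is kept: 74 recruited less 10% leaves 66.6 per group, against 67.3 required. If the sponsor wants 80% power at equal rates of 46.51%, a margin of 0.15 needs 174 per group before dropout, so that choice should be made openly.
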